### Gamification

The use of game-like elements such as progress bars, badges, and rewards has been shown to increase user motivation and adherence in digital health interventions. These strategies leverage principles of intrinsic motivation, offering visual reinforcement and a sense of accomplishment as users complete tasks. When implemented thoughtfully, gamification can help sustain user engagement over time, especially in self-guided programs.

In our previous work, we explored the application of gamified tools to promote physical activity through a social, multiuser platform. This study highlighted the promise and limitations of these techniques in health behavior change [60]. In the current study, gamification is implemented through a dynamic progress bar that visually tracks user progress, reinforcing engagement through motivational feedback, and awarding badges for completing sessions and passing session quizzes.

### Our Prior Work

We have experimented with nudges and prompts in the past. In our previous 3-arm randomized controlled trial (RCT) [24], arm 1 featured a member home page without nudges or prompts. Arm 2 featured a home page with a tip-of-the-day section. Arm 3 featured a home page with a tip-of-the-day section and a to-do checklist.

Control arm members (1788/13,224, 13.52%) completed an average of 1.5 course components. Arm 2 members (865/13,224, 6.54%) clicked on 5% of tips and completed an average of 1.8 course components. Arm 3 members (1914/13,224, 14.47%) clicked on 5% of tips, completed 2.7 of 8 to-do checklist items, and an average of 2.11 course components. Completion rates in arm 2 were greater than those in arm 1 (*z* score=3.37; *P*<.001), and completion rates in arm 3 were greater than those in arm 1 (*z* score=12.23; *P*<.001). Engagement in all 8 components in arm 3 was higher than that in arm 2 (*z* score=1.31; *P*<.001).

Further analysis confirmed that behavioral economics techniques, such as nudges and prompts, significantly enhance engagement in digital health interventions. Specifically, users in the nudge + prompt condition (arm 3) were 93% more likely to engage compared to those in the control group (arm 1), as indicated by an odds ratio of 1.93 (95% CI 1.71-2.17; *P*<.001). This increase in engagement was reflected across multiple platform activities, including self-assessments, goal setting, and content interaction.

However, while these findings validate the effectiveness of nudges and prompts, the study did not explore how individual-level factors shaped these outcomes. Specifically, we did not examine how the intersection of demographic characteristics and cognitive or behavioral phenotypes influenced engagement, if individual engagement followed properties of power laws [61], or if we could leverage economic tools such as the Gini coefficient to plot participation inequality [62].

Understanding these patterns is important for optimizing future interventions for full personalization and maximizing the effectiveness of digital health tools.

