### Randomization

Participants will be randomly assigned to one of the following six arms, as presented in Figure 2:

Arm 1 (baseline control): directive tips only and no to-do checklist.Arm 2: directive tips + social proof tips and no to-do checklist.Arm 3: directive tips + social proof tips + present bias tips and no to-do checklist.Arm 4: directive tips + to-do checklist.Arm 5: directive tips + social proof tips + to-do checklist.Arm 6: gamification (progress bars) + to-do checklist.

Participants will be randomly assigned to one of the six experimental arms using computer-generated randomization in a 1:1:1:1:1:1 ratio. Randomization will be conducted at the point of user registration, ensuring equal probability of assignment to any condition. No stratification or blocking will be used, as randomization is expected to produce comparable groups given the planned sample size. Randomization will be logged automatically by the system to ensure reproducibility and allocation integrity.

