### Power and Sample Size

The primary outcome of interest is engagement, measured through click-through rates, session duration, and to-do checklist completion rates across the 6 experimental arms. These metrics allow us to assess how different combinations of prompts and gamification elements affect user behavior. This will help us determine which strategies are most effective for sustaining participation in self-guided programs.

The study is designed to detect small to moderate effect sizes in engagement differences between intervention groups. Expected effect sizes range from Cohen f=0.1 (small) to f=0.25 (moderate). Our goal is to obtain a power of 80% (β=.20) and a significance level of .05 (α) to ensure adequate sensitivity in detecting meaningful differences between groups.

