#### Sample Size Calculation for ANOVA

Given that engagement metrics will be compared across 6 arms, a one-way ANOVA test was used to estimate the required sample size. For a small effect size (f=0.1), approximately 86 participants per arm (a total of 516 participants) are required. For a moderate effect size (f=0.25), approximately 28 participants per arm (a total of 168 participants) are required. These calculations assume normality of residuals and homogeneity of variance for ANOVA-based analysis. Chosen effect sizes are based on prior research in digital health engagement studies [94-96]. In our prior RCT [23,24], engagement data were analyzed using mixed-effect logistic regression, which does not rely on these assumptions.

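### At 600 users the trial has 80% power only from about f=0.15, while the sponsor's own prior tips v tips + checklist result points to about f=0.07-0.10 for the one contrast repeated here

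*Protocol article*

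**What the plan says.** Power and Sample Size presents the trial as able to detect small to moderate effects: "Expected effect sizes range from Cohen f=0.1 (small) to f=0.25 (moderate"). The target is stated as "Our goal is to obtain a power of 80% (β=.20) and a significance level of .05 (α"). Sample Size Calculation for ANOVA gives the source of the range, "Chosen effect sizes are based on prior research in digital health engagement studies", and the requirement at its lower end: "For a small effect size (f=0.1), approximately 86 participants per arm (a total of 516 participants) are required". The recruitment target is 600 users, 100 per arm, with 15% attrition said to be allowed for.

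Our Prior Work describes a three-arm trial by the same team in which "arm 1 featured a member home page without nudges or prompts". The other two arms were tips, and tips plus a checklist:
- The result given for the tips arm is "Arm 2 members (865/13,224, 6.54%) clicked on 5% of tips and completed an average of 1.8 course components".
- For the arm that added a checklist, the corresponding result is "Arm 3 members (1914/13,224, 14.47%) clicked on 5% of tips, completed 2.7 of 8 to-do checklist items, and an average of 2.11 course components".

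The prompt-free arm (1,788 members) averaged 1.5 components. The reported z scores are 3.37 (arm 2 v 1), 12.23 (arm 3 v 1) and 1.31 (arm 3 v 2, printed with P<.001). The odds ratio of 1.93 is for arm 3 against arm 1.

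The control in the present trial is different: "Arm 1 (baseline control): directive tips only and no to-do checklist". Every one of the six arms has tips, a checklist or both. The Hypothesis section draws on the previous study to expect more engagement in the checklist arms.

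**The concern.** The hypothesis about the checklist rests on the sponsor's previous trial, but the effect size does not. The previous trial's large effect came from a comparison with a page that had no prompts, and the present trial has no such arm. The contrast that does recur is arm 1 (directive tips) against arm 4 (directive tips plus checklist). If the prior difference there was at or below the smallest effect the plan expects, the 80% power statement gives false comfort for that contrast. A non-significant checklist result could then be reported as no effect, although the trial was unlikely to detect an effect of the size already observed.

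**Working it through.** **1. The plan's own figures.** One-way ANOVA with six groups, alpha 0.05, noncentral F with λ = N·f² and df 5 and N−6:
- f=0.1 needs 215 per arm (1,290), not 86 (516). Power at 516 is 37%.
- f=0.25 needs 36 per arm (216), not 28 (168). Power at 168 is 68%.

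The printed sample sizes are not reproduced. That is a separate error. Correcting it would not show whether the effect range suits the contrasts in this trial.

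**2. SDs implied by the prior trial.** No SD is reported. If the z scores compare mean components completed between two arms, then d = z·√(1/n₁+1/n₂) and SD = mean difference / d.
- Arm 3 v 1: d = 12.23·√(1/1914+1/1788) = 0.402; SD = 0.61/0.402 = 1.52.
- Arm 2 v 1: d = 3.37·√(1/865+1/1788) = 0.140; SD = 0.30/0.140 = 2.15.

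**3. Prior effects as f = d/2.**

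| Prior contrast | Present here? | f |
|---|---|---|
| Tips + checklist v prompt-free | No | 0.20 (from z); 0.14 (means, SD 2.15); 0.18 (from OR 1.93, d = ln(1.93)·√3/π = 0.363) |
| Tips v prompt-free | No | 0.07 (from z) to 0.10 (means, SD 1.52) |
| Tips + checklist v tips | Yes, arm 4 v arm 1 | 0.31/2.15/2 = 0.072; 0.31/1.52/2 = 0.102 |

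**4. Why z=1.31 is not used for the last row.** It corresponds to a two-sided P of 0.19, not P<.001. The means with these SDs imply z = 0.31/(SD·√(1/1914+1/865)), which is 3.5 to 5.0. That agrees with the printed P value and not with the printed z.

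**5. Power of the present trial.** If the checklist alone has an effect and three of the six arms (4 to 6) carry it, the six-arm f is also d/2.

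| f | N=600: λ, power | N=510 (600·0.85): λ, power |
|---|---|---|
| 0.072 | 3.11, 23% | 2.64, 20% |
| 0.100 | 6.00, 43% | 5.10, 37% |
| 0.102 | 6.24, 45% | 5.31, 38% |

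Eighty percent power is reached at f=0.147 with 600 users and at f=0.159 with 510. A direct comparison of arm 4 with arm 1, 100 users each, has 17% power at f=0.072 and 30% at f=0.102.

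**The case against.** The best defence is that the derived range is fragile and narrow in scope. No SD or test is reported, and the two implied SDs differ by about 40%, which casts doubt on a common-SD comparison of means. An SD of 1.25 would give f=0.124, inside the planned range. At its upper end the derived value (0.102) meets the planned minimum, where power (45%) is almost the same as at the plan's own f=0.1 (43%). Components completed is a secondary outcome here. Only arm 4 v arm 1 repeats the prior contrast. All of this stands. It limits the point to the checklist contrast and to wording such as at or below the bottom of the range. It does not rescue the 80% claim, which fails at f=0.1 whatever the prior trial showed.

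Stronger readings are tempting, but the documents do not support them:
- **The prior checklist effect was only about f=0.03.** That figure follows from z=1.31 alone, which conflicts with its own P value and with the reported means. That z score is also attached to a differently worded measure (engagement in all eight components).
- **The checklist had no effect on the primary outcome, because tip clicks were 5% in both arms.** Primary and Secondary Outcomes also counts clicks on checklist items, and prior arm 3 members completed 2.7 of 8.
- **f=0.1 means a doubling of a 5% click rate, or some fixed detectable click rate.** Such conversions depend on the number of tips shown per user, which is not given.
- **The whole f=0.1 to 0.25 range is wrong for all six arms.** The prior trial, as described, gives no result on social proof against directive tips, on present bias tips or on gamification, and the cited outside studies cannot be checked here.

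**Conclusion.** The point holds in this limited form. For the one contrast carried over from the sponsor's previous trial, the reported means suggest about f=0.07 to 0.10, at or below the lowest effect the plan expects. The larger prior effect belongs to a comparison that this trial does not contain. At 600 users the planned ANOVA has about 23% to 45% power there (20% to 38% after attrition), and the design reaches 80% only at about f=0.15 to 0.16. The claim that the trial is designed to detect f=0.1 with 80% power is therefore wrong as written.

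The f range assumes that the two usable z scores compare mean components completed and that their implied SDs apply to arm 3 v 2. The six-arm power also assumes that the checklist effect is the same in arms 4 to 6 and that nothing else differs. The statement that 600 users give 43% power at f=0.1 needs none of these assumptions. All power figures are for the one-way ANOVA on which the plan bases its sample size.

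**What to change.** In Power and Sample Size and Sample Size Calculation for ANOVA:

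1. Keep 600 users. State that the six-arm ANOVA has 80% power for about f=0.15 (600 analysed) to f=0.16 (510 analysed), and 43% or 37% at f=0.1.
2. Remove the claim that the trial is designed to detect small effects (f=0.1), and correct the printed per-arm numbers at the same time.
3. Cite the prior tips v tips + checklist result, about f=0.07 to 0.10 on components completed, as the internal evidence for the checklist contrast. Mark it as derived, and give its power (about 23% to 45% with 600; 20% to 38% with 510).
4. State that a null checklist result would not rule out an effect of that size.
5. Do not extend this range to the social proof, present bias or gamification contrasts. Do not use the z=1.31 value, or click-rate conversions that need an unstated number of tips per user.

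The sponsor holds the prior data and could replace the derived range with the observed SD and test result. The cost is protocol wording only: no extra participants, but a less favourable power statement.

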### Objective

The primary objective is to analyze user engagement with randomized tips and to-do lists within a resiliency course tailored for Ukrainian refugees affected by the ongoing humanitarian crisis. Insights will inform the development of an AI-based personalization system to optimize engagement and address behavioral health challenges. This approach is designed to improve real-world adherence while maintaining cultural relevance. Secondary objectives include identifying demographic and behavioral predictors of engagement and creating scalable, culturally sensitive nudging [63,64] and intervention models. These insights will also inform future adaptations of the intervention across languages and cultural contexts.

Since there is a paucity of published research in this area [65-67], our unique dataset holds the potential to customize user experiences and transform digital engagement by leveraging behavioral phenotypes and machine learning. Few studies have explored the predictive potential of behavioral cues in real-world digital health environments. This trial is designed to fill that gap and generate data suitable for training scalable AI-driven models.

## Methods

### Digital Health Platform

The digital health platform used in this study is managed by Evolution Health. EvolutionHealth.care is an evidence-based digital health content provider that features courses based on behavior change techniques, including cognitive behavioral therapy (CBT), stages of change, structured relapse prevention, harm reduction, and quizzes based on brief intervention.

The platform offers interactive courses and quizzes for mental health issues, addiction issues, and obesity. It also contains a moderated community based on social cognitive theory.

Limited memberships are available to individuals who register through the organization’s free-to-consumer program. Full memberships are available through white-label instances licensed to employers, insurance companies, employee assistance programs, educational institutions, nonprofit organizations, for-profit health care organizations, and individual therapists.

### The Intervention

Shared Strength (Спільна Сила) is a self-guided interactive behavior change treatment course based on traditional evidence-based treatments (Table 2). It draws from multiple therapeutic frameworks, including CBT, motivational interviewing, and social cognitive theory. The goal is to provide users with a flexible, culturally sensitive, interactive course that supports emotional resilience and behavior change.

Other interactive courses in the Evolution Health platform have been extensively examined in the literature [10,23,24,61,62,68-90]. Shared Strength mirrors its structure and design (Table 3). This consistency enables us to leverage existing platform infrastructure and previous research insights while applying new engagement strategies.

**Table 2 table2:** Theoretical constructs and evidence-based components.

Theoretical construct	Shared Strength (Спільна Сила)
Brief intervention	✓
Cognitive behavioral therapy	✓
Gamification	✓
Health belief model	✓
Motivational interviewing	✓
Social cognitive theory	✓
Targeting and tailoring	✓

**Table 3 table3:** Main course components.

Course component	Shared Strength (Спільна Сила)
Avatar upload	✓
Course completion certificate	✓
Course worksheets	✓
Gamified CBT^a^ course	✓
Getting started video	✓
Goals exercise	✓
Moderated community	✓
Private messaging	✓
Statistics extranet (for corporate clients)	✓
Tailored depression and anxiety test	✓
Therapist extranet	✓

^a^CBT: cognitive behavioral therapy.

### Course Content Overview

Shared Strength (Спільна Сила) contains nine interactive sessions. Each session is designed to foster emotional resiliency using evidence-based strategies drawn from CBT, behavior change theory, and supportive self-help principles. The structure allows participants to move at their own pace while reinforcing learning and self-efficacy. Key session themes include (1) understanding emotional responses to displacement, (2) managing anxiety and low mood, (3) setting personal goals and building hope, (4) practicing mindfulness and grounding techniques, and (5) strengthening connections and community.

Each session includes short readings and interactive tools, such as goal setting, a resiliency diary, to-do checklists, and a summary quiz to reinforce learning. Users progress at their own pace.

### Cultural Adaptation Process, Participatory Design, and Interdisciplinary Collaboration

Following best practice [63,91-93], the Ukrainian version of the Shared Strength course is undergoing cultural adaptation. This process involves collaboration with a bilingual mental health professional and displaced Ukrainian software developers, each bringing insight into the lived experiences of displacement. The adaptation process includes (1) linguistic translation of all English course material, including prompts and tips; (2) contextual revision of examples, tips, and imagery to align with Ukrainian cultural norms and displacement-related stressors; (3) tone and voice refinement to reflect empathy, autonomy, and strength-based messaging in line with Ukrainian cultural communication preferences; (4) technical development and coding by displaced Ukrainian engineers, ensuring both usability and cultural sensitivity; and (5) clinical accuracy: a Ukrainian psychiatrist with experience in delivering CBT-based behavioral interventions and developing digital health tools will review the content.

In addition to linguistic and cultural adaptation, all content is written using plain-language principles to support accessibility for users with varying literacy levels. Usability testing is being conducted with displaced Ukrainian collaborators to ensure the platform is intuitive and accessible for individuals experiencing stress or trauma. This dual approach enhances both comprehension and user trust.

### Recruitment and Participants

Participants will be recruited through partnerships with nonprofit organizations, digital outreach campaigns, and community organizations. Enrollment will occur via the EvolutionHealth.care platform, where participants will be randomized automatically upon sign-up using a computer-generated sequence, ensuring unbiased allocation.

As part of our ethical commitment to accessibility and user privacy, no personal or demographic data will be collected to identify users as displaced or Ukrainian. While this is a limitation, our dissemination model mitigates this concern by partnering with refugee-serving organizations and providing them with custom-branded course instances (eg, “https://YourOrg.EvolutionHealth.care”) or masking their instance with a full URL (eg, “https://YourChosen URL.extension”).

This strategy enables us to reach targeted communities through trusted channels, reducing the likelihood of sample contamination while maintaining an open-access structure that supports real-world scalability and humanitarian distribution. It allows refugee-serving organizations to promote the intervention under their trusted branding. This partnership model combines targeted outreach with the scalability of digital delivery.

### Randomization

Participants will be randomly assigned to one of the following six arms, as presented in Figure 2:

Arm 1 (baseline control): directive tips only and no to-do checklist.Arm 2: directive tips + social proof tips and no to-do checklist.Arm 3: directive tips + social proof tips + present bias tips and no to-do checklist.Arm 4: directive tips + to-do checklist.Arm 5: directive tips + social proof tips + to-do checklist.Arm 6: gamification (progress bars) + to-do checklist.

Participants will be randomly assigned to one of the six experimental arms using computer-generated randomization in a 1:1:1:1:1:1 ratio. Randomization will be conducted at the point of user registration, ensuring equal probability of assignment to any condition. No stratification or blocking will be used, as randomization is expected to produce comparable groups given the planned sample size. Randomization will be logged automatically by the system to ensure reproducibility and allocation integrity.

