#### Behavioral Prompts

Behavioral prompts are cues specifically designed to encourage a specific task [58]. In this study, we will use 2 types of behavioral prompts anchored in nudge theory: daily tips and a to-do checklist (Table 1). These prompts are intended to support self-guided action, reinforcing positive behavior without requiring direct human intervention.

An effective approach for boosting user involvement in digital health interventions may be offered by analyzing combinations of behavioral prompts that users engage with. Through machine learning techniques, the dataset emerging from this study may provide insight into which and what prompts work best with specific demographics and usage patterns [59]. By customizing interventions to meet the unique needs of every user, this integrated approach might increase the possibility of long-term behavior change and better health outcomes.

**Table 1 table1:** Example nudges and prompts.

Delivery format	Content type	Example from our study
Tip	Directive content	Express yourself by uploading your image!
Tip	Social proof	Many members have similar goals to yours. Reviewing other members’ goals can help you reach your goal.
Tip	Present bias	Feel better sooner by learning from others. Read what others have posted in the community.
Prompt	To-do checklist	Watch the getting started video.
Visual element	Gamification	A progress bar fills as users complete sections of the course.

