### Multiarm Trial Rationale

The six study arms were developed to explore the individual and combined effects of behavioral prompts grounded in behavioral economics, to identify which strategies most effectively enhance engagement in a digital resiliency program. Each arm includes a specific configuration of tips, checklists, or gamification elements intended to test distinct motivational mechanisms. This design enables comparative analysis across different engagement strategies while remaining operationally feasible. These components tested include (1) directive tips, grounded in the theory of implementation intentions, which provide straightforward, actionable guidance; (2) social proof tips, which leverage peer effects by referencing the behavior of others to encourage participation; (3) present bias tips, designed to counteract temporal discounting by emphasizing short-term benefits of engagement; (4) to-do checklists, which introduce structured goals and progress-tracking to increase adherence; and (5) gamification, which builds intrinsic motivation through visual indicators of advancement and progress feedback.

While a full factorial design could have explored all possible combinations of these interventions, the current 6-arm structure is a deliberate balance between conceptual rigor and practical feasibility. This structure enables comparative analysis across a diverse set of nudge combinations without creating an unmanageable number of trial arms. It was also informed by operational constraints and the need for meaningful data distribution across arms.

Our study design is also a foundational step toward developing a predictive analytics dataset. The behavioral engagement data collected through the six arms will be used to build baseline models that inform AI-driven personalization strategies. Future iterations of the course will be updated with tailored nudges based on user profiles, and new user data will be used to validate and refine the models. We chose the current design to generate sufficient diversity and volume in behavioral data to create a baseline for our long-term, adaptive research agenda.

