### Data Collection

The Evolution Health platform is equipped with a custom data collection interface and reporting mechanism. Data will be collected for each member who is randomly assigned to the experiment, and all data are self-reported. Information on age and self-identified gender will be collected at registration or during secure sign-on across various white-label instances.

The custom database will also track behavioral engagement with each tip and to-do item randomly presented to users, including whether a tip was displayed, whether it was clicked, and whether the user completed the corresponding course component.

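### Arms 2 v 1, 3 v 2 and 5 v 4 compare tip mixes or tip volumes, so they do not isolate the effect of a tip type on user-level clicks

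*Protocol article*

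**What the plan says.** The Randomization section of the protocol article gives the control as "Arm 1 (baseline control): directive tips only and no to-do checklist", arm 2 as "directive tips + social proof tips and no to-do checklist" and arm 3 as "directive tips + social proof tips + present bias tips and no to-do checklist". Arms 4 and 5 repeat the content of arms 1 and 2 with a to-do checklist. No arm shows social proof or present bias tips alone.

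The Multiarm Trial Rationale says that the arms were built to "explore the individual and combined effects of behavioral prompts", and the Methods part of the Abstract has comparisons between arms serve to evaluate each component.

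On delivery, Behavioral Prompts speaks of "daily tips and a to-do checklist", and Data Collection says that the database tracks "behavioral engagement with each tip and to-do item randomly presented to users", recording display and click. The tip-of-the-day layout appears under Our Prior Work, as a description of the previous trial.

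Under Primary and Secondary Outcomes, the primary outcome is a yes/no click by a user on a tip, a kind of tip or a checklist entry. Click rate as a proportion is secondary and pools tips with checklist items.

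**The concern.** The arms are written as sums, which invites reading arm 2 v 1 as the effect of adding social proof tips, arm 3 v 2 as that of adding present bias tips, and arm 5 v 4 as that of adding social proof when a checklist is present. For that reading, the background of directive tips and the total number of tips would both have to stay the same across arms. They cannot both do so: either the new type takes displays from the old ones, or it brings extra displays.

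A type-specific click does not help across arms. Arm 1 shows no social proof tip, so the only tip outcome common to arms 1, 2 and 3 is a click on any tip. A null result in arm 2 v 1 could then be read as social proof having no effect, when it may only mean that social proof does as well as the directive tip it replaced. That reading would pass into the personalization models that the trial is meant to feed.

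**Working it through.** The plan states no figure for these contrasts, so there is none to reproduce. The check follows both possible delivery schemes.

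**Inputs.** The click rate per displayed directive tip is d = 5%, borrowed from the overall tip click rate under Our Prior Work (an assumption). The social proof rate s and present bias rate p are varied (assumptions). The number of displays, or days, is T = 10, with 5 and 20 as alternatives (assumption). There are 100 users per arm (Sample Size Justification). Power is for a two-sided two-proportion z test at 0.05.

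**Scheme A: one tip per day from the arm's pool, equal shares.** Directive tips make up 100%, 50% and 33% of displays in arms 1, 2 and 3. Click rates per tip are d, (d+s)/2 and (d+s+p)/3, so:
- arm 2 − arm 1 = (s − d)/2
- arm 3 − arm 2 = p/3 − (d+s)/6, negative when p < (d+s)/2
- arm 3 − arm 1 = [(s − d) + (p − d)]/3, negative when the mean of s and p is below d

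Arm 5 − arm 4 follows the first line for clicks on tips.

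Per tip:
- s = p = 5%: both contrasts with control are 0.
- s = 10%, p = 5%: arm 2 is +2.5 points and arm 3 is +1.7 points against control. The 5-point advantage of social proof shows as a half and a third.

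Any-click for users who respond alike is 1 − (1 − rate)^T. At T = 10:

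| s, p | Arm 1 | Arm 2 | Arm 3 | Power, 2 v 1 |
|---|---|---|---|---|
| 5%, 5% | 40.1% | 40.1% | 40.1% | no difference |
| 7.5%, 5% | 40.1% | 47.6% | 45.2% | 18% |
| 10%, 5% | 40.1% | 54.1% | 49.8% | 51% |
| 5%, 2.5% | 40.1% | 40.1% | 34.7% | no difference |

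In the second row arm 3 is 2.4 points below arm 2, although present bias tips match the control's tips; it is still about 5 points above control. In the last row arm 3 is below control, with power of about 12% for arm 3 v 1. The directions are the same at T = 5 and T = 20.

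**Users who differ.** Suppose half click only directive tips and half only social proof tips, each at 10%. Both types then average 5%, and the click rate per tip is 5% in both arms. Any-click is 0.5 × (1 − 0.9^10) = 32.6% in arm 1 and 1 − 0.95^10 = 40.1% in arm 2. At T = 20 it is 43.9% v 64.2%. Equal average effectiveness therefore gives zero on clicks per tip, but not always on any-click.

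**Scheme B: a separate daily slot for each type.** With every type at 5% and T = 10 days, arms 1, 2 and 3 show 10, 20 and 30 tips. Any-click is 1 − 0.95^10 = 40.1%, 1 − 0.95^20 = 64.2% and 1 − 0.95^30 = 78.5%. The arms differ widely although the types are identical in effect.

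**The case against.** The strongest reply is that one tip per day from a pool is nowhere stated for this trial. It is inferred from the daily tips, their random presentation and the previous trial's layout, and a condensed article may leave such mechanics to a fuller document. That stands: the missing delivery rule is not itself the fault. The point does not depend on it, because the other scheme mixes tip type with tip volume.

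The plan also helps itself in part. The primary outcome mentions kinds of tip, displays and clicks are logged, the control is openly an active one, the rationale also speaks of combinations, and the arm hypotheses concern arms 5 and 6. So the data to answer the question will exist. What remains is that the text assigns the evaluation of each component to comparisons between arms and ties no per-display analysis to tip type.

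Two stronger readings are tempting. A reader might infer that the contrast with control is always zero for an equally effective type. On any-click this fails when users differ in what they respond to, which is the trial's own premise. A reader might also infer that arm 3 is set up to look harmful. Against control that requires the added types to average below directive tips. Against arm 2, the 2.4-point deficit above would reach significance only about 6% of the time at 100 per arm.

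**Conclusion.** The concern holds in this limited form: arm 2 v 1, 3 v 2 and 5 v 4 do not isolate the effect of a tip type on the user-level click outcome. With pooled delivery and equal shares, a social proof advantage over directive tips appears at half its size in arm 2, and an equally effective type gives zero on clicks per tip. With separate slots, identical types can produce 40.1%, 64.2% and 78.5%. The percentages rest on the borrowed 5% rate, the assumed number of displays, independent clicks and, except where stated, users who respond alike. The algebra for pooled delivery needs only equal shares and rates per type that do not change between arms. The documents do not settle which scheme applies, and they do not support a claim that the arms will mislead in a particular direction.

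**What to change.** In Randomization and the Multiarm Trial Rationale, describe arm 2 v 1, 3 v 2 and 5 v 4 as comparisons of tip mixes against an active directive-tip comparator (with the checklist in arm 4), and say that a null result does not show a tip type to be ineffective. Stating how many tips are shown and how they are drawn would let readers see which scheme applies.

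Estimate tip-type effects from the display log: one record per display, with the type shown and clicked or not as the outcome, within arms 2, 3 and 5 and clustered by user. The generalized estimating equations already planned under Sample Size for Repeated Measures would serve. This targets s − d directly rather than half of it, and the number of displays becomes the denominator. The comparison is randomized if the random presentation covers tip type.

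Holding the number of directive displays equal across arms is not a remedy: arms 2, 3 and 5 would then show more tips in total, and type would be confounded with volume.

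The cost is some rewording and one extra analysis of data already logged. The price is a weaker claim from the arm contrasts about individual tip types.
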